### Sample size

Analogous to previous studies about the effect of preventive interventions in volleyball [7] and in other sports [8, 9], the assumption is that a 40% injury reduction will be achieved over one season in the intervention group by comparison to the control group. To achieve 80% power with a significance level of 0.05, an injury prevalence estimate of 0.25 in the control group and a loss to follow-up among players of 15% over one season (no multiple cluster randomization), the sample size calculation reveals that 640 volleyball players are needed in the study [4]. Consequently, we will strive to enroll 64 teams (average of 10 players per team) assigned either to the intervention or the control group (equal number of 32 teams in each group). The teams within the intervention and control groups will be matched according to their competition level.

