**Methods:**

A randomized prospective controlled trial with a follow-up period of one volleyball season will be conducted. Participants will be healthy recreational adult volleyball players (18 years of age or older) practicing volleyball (training and/or match) at least twice a week. The intervention (‘VolleyVeilig’) consists of a warm-up program based on more than 50 distinct exercises (with different variations and levels). The effect of the intervention programme on the occurrence of injuries will be compared to volleyball as usual. Outcome measures will be incidence of acute injury (expressed as number of injuries per 1000 h of play) and prevalence of overuse injuries (expressed as percentage).

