### Objective and hypothesis

The objective of the study is to evaluate the effectiveness of the developed intervention (‘VolleyVeilig’) on the one-season occurrence of finger/wrist, shoulder, knee and ankle injuries among recreational adult volleyball players. Analogous to previous studies about the effect of preventive interventions in volleyball [7] and in other sports [8, 9], the hypothesis of this study is that the developed intervention will lead to a 40% reduction of the number of musculoskeletal injuries over the one-season follow-up in the intervention group by comparison to the control group.

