### Intervention

The intervention ‘VolleyVeilig’ (in Dutch) is made available exclusively to the participants within the intervention group, aiming to prevent or reduce the occurrence of finger/wrist, shoulder, knee and ankle injuries among adult recreational volleyball players. The intervention consists of a warm-up program including more than 50 distinct exercises (with different variations and levels) that should be conducted at least twice a week prior to any volleyball activity (training or match) [10]. The intervention is divided into 6 phases, each lasting 5 to 6 weeks (accordingly to a typical volleyball season), providing volleyball coaches every week with a new warm-up program that shows progressive increments in terms of intensity, frequency, duration and/or complexity. Each warm-up program lasts 15 min and is divided into a preparatory cardiovascular warm-up (2 to 3 min), core stability exercises (2 to 3 min; for instance straight plank), exercises principally directed towards the prevention of knee injuries (4 to 5 min; for instance squat), and exercises principally directed towards the prevention of shoulder injuries (4 to 5 min; for instance external rotation strength with resistance elastic). The exercises directed towards the prevention of ankles injuries (for instance one legged stance) are embedded within each warm-up program. All warm-up programs of the intervention are overseen by the coaches, being available through a website and an application for smartphone/tablet (automatic synchronisation) that are accessible with a username and password. Information and instructions about the exercises are available as texts and video’s (including voice-over). Illustrations of the website and application for smartphone/tablet as well as examples of exercises within the intervention are presented in Fig. 2.

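### The 80% power is calculated for a single season injury proportion that neither planned test compares, and no primary outcome is named

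*Protocol article*

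**What the plan says.** All places are in the protocol article.

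- **Objective and hypothesis.** The objective concerns the "one-season occurrence of finger/wrist, shoulder, knee and ankle injuries among recreational adult volleyball players". The hypothesis in the same section is wider: a "40% reduction of the number of musculoskeletal injuries over the one-season follow-up", with no split by injury type or site.
- **Sample size.** The calculation is introduced with "To achieve 80% power with a significance level of 0.05". It assumes "an injury prevalence estimate of 0.25 in the control group", that "a 40% injury reduction will be achieved over one season in the intervention group", and "a loss to follow-up among players of 15% over one season (no multiple cluster randomization". The result is 640 players, as 64 teams of about 10, with 32 teams per group.
- **Abstract, Methods.** "Outcome measures will be incidence of acute injury (expressed as number of injuries per 1000 h of play) and prevalence of overuse injuries". Two outcomes are listed and neither is called primary.
- **Statistical analysis.** The acute comparison is a Cox regression. The overuse comparison takes the mean of the 2-weekly prevalences and uses a t-test and/or Mann-Whitney test. Neither test carries a stated restriction to the four sites. The section on exposure and injury monitoring shows that the questionnaire records injury location.

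**The concern.** A power statement is useful only if it belongs to a test that will be run. Here the number of players comes from one season proportion, while the conclusions will come from two different quantities. One is an acute event rate over exposure time. The other is a repeatedly measured 2-week prevalence, which is a different scale from the proportion of players injured over a season.

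If acute injuries make up only part of the 25%, the acute test has fewer events than the calculation supposed. A null acute result could then be read as evidence that the programme does not work when the test had little chance of detecting the assumed effect. With no primary outcome named, it is also open which result decides a question that the article links to nationwide implementation.

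**Working it through.** **Inputs from the Sample size section.** Control proportion p1 = 0.25. Relative reduction 40%, so p2 = 0.25 × 0.6 = 0.15. Power 80%, alpha 0.05 (two-sided assumed, as the side is not stated), 15% loss, equal groups.

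**Step 1: reproduce 640.** Pooled two-proportion formula, with mean proportion 0.20:

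n = [1.96·√(2·0.20·0.80) + 0.842·√(0.25·0.75 + 0.15·0.85)]² / 0.10² = (1.109 + 0.472)² / 0.01 ≈ 250 per arm.

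Continuity correction: n' = (n/4)·[1 + √(1 + 4/(n·0.10))]² = 269.6, so 270 per arm.

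Loss: 270/0.85 = 317.6, so 318 per arm and 636 in total, or 64 teams of 10 = 640. Without the continuity correction the total is 590. An events-based calculation with hazard ratio 0.60 gives about 712 (Schoenfeld) or 741 (Freedman). The stated figure is thus that of one comparison of 25% with 15%, and its arithmetic is sound.

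**Step 2: look for that comparison in the analysis.**

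| Place | Quantity | Injury type | Sites |
|---|---|---|---|
| Objective | season occurrence | not separated | four named |
| Hypothesis | number of injuries | not separated | not restricted |
| Sample size | season proportion, 0.25 to 0.15 | not separated | not stated |
| Test 1 | acute incidence, Cox | acute only | not stated |
| Test 2 | mean 2-week prevalence | overuse only | not stated |

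No row under the analysis matches the sample-size row.

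**Step 3: power of the acute comparison at the planned size.** Evaluable players per arm: 640 × 0.85 / 2 = 272. Let s be the share of the 25% that is acute. The article does not give s, so it is varied as an assumption. Then a = 0.25s, b = 0.15s, m = (a + b)/2, and

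power = Φ{[(a − b) − 1.96·√(2m(1 − m)/272)] / √([a(1 − a) + b(1 − b)]/272)}.

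Example, s = 0.5: a = 0.125, b = 0.075, difference 0.050, null SE 0.02572, alternative SE 0.02564. So (0.050 − 1.96 × 0.02572)/0.02564 = −0.016, and Φ = 0.49.

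As a check on the Cox scale: events = 272(a + b), HR = ln(1 − b)/ln(1 − a), power = Φ(½·√events·|ln HR| − 1.96).

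| Acute share s | Control / intervention risk | Power, two proportions | Events | Power, Cox (Schoenfeld) |
|---|---|---|---|---|
| 100% | 0.250 / 0.150 | 83% | 109 | 85% |
| 80% | 0.200 / 0.120 | 72% | 87 | 74% |
| 70% | 0.175 / 0.105 | 65% | 76 | 67% |
| 50% | 0.125 / 0.075 | 49% | 54 | 51% |
| 30% | 0.075 / 0.045 | 31% | 33 | 32% |

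The two methods agree closely, so the loss comes from splitting the outcome and not from using Cox regression. If the 40% is read as a hazard ratio of 0.60, Cox power is 77% at a 100% share and 47% at 50%. All figures ignore clustering by team.

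**Step 4: power of the overuse comparison.** This needs a 2-week prevalence, its standard deviation and the correlation within players over time. None is stated, so no figure can be given.

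**The case against.** The strongest reply is that the article never says the 0.25 means any injury. It says only injury prevalence and cites a source not at hand. If that figure is the season risk of acute injury, the acute test has about 83% to 85% power (77% with hazard ratio 0.60), and the shortfall all but disappears. This stands as a limit on the size of the problem: the loss is conditional on the acute share. It does not remove the mismatch. The text does not tie 0.25 to acute injury, the hypothesis on the total number of injuries points the other way, and the overuse test would still have no power basis.

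A second reply is that site restriction and multiplicity are often left to the full protocol or analysis plan. That is fair. The article does not state that all sites are pooled, only that no restriction is given. But a later plan cannot make the 640 apply to a test for which it was not computed.

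A third is that the article gives a reason for separating the outcomes, since it regards repeated prevalence as the better measure for overuse injury. That is a good reason to keep the overuse measure, but not a reason to leave it without a power statement.

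A reader might also infer more than the text supports:

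- **That the programme does not train the finger/wrist.** Ankle work is described with "The exercises directed towards the prevention of ankles injuries (for instance one legged stance) are embedded within each warm-up program" and finger/wrist work is not mentioned. But the article describes more than 50 exercises through examples only, refers elsewhere for the content, and has a figure that is not shown.
- **That untargeted injuries dilute the effect by a calculable amount.** This needs an invented share of non-responsive injuries, and the hypothesis already places the 40% on the total.
- **That the false-positive rate is nearly doubled.** No rule says that either test alone is enough to claim success, and the two outcomes need not be independent.
- **That power should be computed for the smaller enrolment given in the Discussion.** That is a separate matter and is not used here.

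**Conclusion.** The point holds in this form: the 80% power belongs to a two-proportion comparison that is not planned, and it is not shown for either planned test. That part rests on the article's own statements and needs no outside figure.

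The size depends on an unknown. Reading the 25% as any injury is natural but not stated. Over an assumed acute share of 100% down to 30%, two-proportion power for the acute comparison runs from 83% down to 31%, and it is already 72% at an 80% share. It would therefore be wrong to say that the acute test is shown to be underpowered. The correct statement is that its power is unknown and falls below target once a material part of the 25% is overuse injury. Restricting the tests to the four sites could only lower the event count further, by an amount the article does not give. The overuse test's power cannot be determined.

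**What to change.** 1. Name one primary outcome tied to the objective and restricted to finger/wrist, shoulder, knee and ankle, using the location data already collected. One option is the first new acute or overuse injury at those sites during the season, with acute incidence and repeated overuse prevalence kept as secondary outcomes. Its drawback is that onset of a gradual injury is known only to a 2-week window.
2. State which injuries and sites the control-group rate covers, with its source, and restate the power for the test that will be used. Do not assume that 25% carries over to the four-site outcome.
3. If acute incidence and overuse prevalence are both kept as primary, state the power for each, including the prevalence, standard deviation and within-player correlation for the overuse test. Control the error rate across the two, for example with Holm.

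The cost is a short derivation of the outcome, a revised calculation with a new event rate, and probably a less favourable stated power. No new data collection is needed.

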### Statistical analysis

Descriptive analyses (mean, standard deviation, frequency, range) will be conducted for the different baseline variables in both study groups. To evaluate the success of the randomization and matching, baseline values will be analysed for differences between the intervention and control group (Chi Square, independent T-tests and/or Mann-Whitney test). Total, training and match incidence of acute injury (and its 95% CI) will be calculated by dividing the number of newly incurred acute injuries (excluding re-injuries) identified during the follow-up by the sum of volleyball exposure (total exposure, training exposure and match exposure) in hours until the first injury [14, 15]. For overuse injuries, prevalence repeatedly measured over time is considered the preferable measure [15]. Therefore, the mean prevalence (expressed as percentage) of overuse injuries repeatedly measured over time will be calculated for each 2-week period by dividing the number of participants reporting an overuse injury during that period by the total number of respondents during the same period. Then, mean prevalence (and its 95% CI) will be calculated by dividing all prevalence rates measured every 2 weeks by the number of 2-week periods. Differences in the incidence of acute injury between the intervention and control groups will be assessed using cox regression analysis (significance level set at *p* < .05; adjusted for age and/or gender). Differences in the prevalence of overuse injury between the intervention and control groups will be assessed by comparing their mean prevalence (independent T-tests and/or Mann-Whitney test). Secondary analyses will be conducted to compare the onset of acute and overuse injury between the intervention and control groups based on three levels of adherence (low, medium, high).

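### Players are enrolled in teams of about 10 under one coach, but the sample size has no design effect and the stated analyses have no allowance for team, so power and precision are overstated by an amount that depends on an unstated ICC

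*Protocol article*

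**What the plan says.** The protocol article (Sample size) fixes the design values: "To achieve 80% power with a significance level of 0.05", "an injury prevalence estimate of 0.25 in the control group", and the assumption that "a 40% injury reduction will be achieved over one season in the intervention group by comparison to the control group". To these it adds "a loss to follow-up among players of 15% over one season (no multiple cluster randomization"), and concludes that "the sample size calculation reveals that 640 volleyball players are needed in the study". No ICC or design effect appears.

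The same section shows that recruitment is by team: "we will strive to enroll 64 teams (average of 10 players per team"), 32 per group. It adds that "The teams within the intervention and control groups will be matched according to their competition level". Participants and recruitment says that players are reached through their coaches. Intervention says that coaches oversee the warm-up. Study design and allocation says that two competition regions are randomised, one to each arm.

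On analysis, the article (Statistical analysis) states: "Differences in the incidence of acute injury between the intervention and control groups will be assessed using cox regression analysis", adjusted for age, gender or both. Mean overuse prevalence is compared by t-test, Mann-Whitney test or both. No team term, frailty or clustered variance is stated for either outcome, and competition level is not among the covariates.

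**The concern.** Teammates share a coach, a warm-up and a competition level, and the coach also reports their exposure. Their injury outcomes are therefore likely to be positively correlated. If so, 10 players from one team carry less information than 10 unrelated players.

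This has two consequences. A sample size that counts players as independent has less power than stated. A test and confidence interval that ignore team are too optimistic. The second matters more, because the results are meant to support nationwide implementation of the programme.

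The remark about multiple cluster randomisation may mean only that a single region is allocated to each arm. Even so, it does not make teammates independent and cannot justify omitting a design effect.

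**Working it through.** **Inputs.** From Sample size: control proportion 0.25; 40% reduction, so 0.15 in the intervention arm; power 80%; significance level 0.05 (sidedness not stated; two-sided reproduces the result); loss 15%; 10 players per team; 640 in total. From the Discussion: 456 players in 46 teams. Assumed, because the article gives none: team ICC of 0.01 to 0.10.

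**Step 1: reproduce 640.** The pooled term is √(2×0.2×0.8) = 0.5657 and the unpooled term is √(0.25×0.75 + 0.15×0.85) = 0.5612.

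- Uncorrected n per arm = (1.96×0.5657 + 0.8416×0.5612)² / 0.1² = 250.
- With continuity correction: (250/4) × [1 + √(1 + 4/(250×0.1))]² = 269.6, so 270 per arm.
- With 15% loss: 270/0.85 = 317.6, so 318 per arm and 636 in total, which rounds up to 64 teams of 10 = 640.

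The stated number is therefore an individual-level one. On this continuity-corrected basis, 640×0.85/2 = 272 analysed per arm gives 80.4% power, so there is no room for a design effect.

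**Step 2: add team.** Players analysed per team: m = 10×0.85 = 8.5. Design effect: DE = 1 + (m − 1)×ICC = 1 + 7.5×ICC. The effective n per arm is 272/DE at 640 enrolled, and 193.8/DE at 456 enrolled (456×0.85/2 = 193.8).

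- Power, without continuity correction: Φ[(0.1×√n − 1.96×0.5657)/0.5612].
- Type I error of a test that ignores team: 2×[1 − Φ(1.96/√DE)].
- Factor by which the interval is too narrow: √DE.

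Example at ICC 0.05: DE = 1.375; 272/1.375 = 197.8; power = Φ[(1.4065 − 1.1087)/0.5612] = Φ(0.531) = 70.2%; type I error = 2×[1 − Φ(1.671)] = 9.5%.

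| ICC | DE | Power, 640 | Power, 456 | Type I error | CI factor |
|---|---|---|---|---|---|
| 0 | 1.000 | 83.2% | 69.3% | 5.0% | 1.00 |
| 0.01 | 1.075 | 80.5% | 66.2% | 5.9% | 1.04 |
| 0.02 | 1.150 | 77.8% | 63.2% | 6.8% | 1.07 |
| 0.05 | 1.375 | 70.2% | 55.6% | 9.5% | 1.17 |
| 0.10 | 1.750 | 59.7% | 46.0% | 13.8% | 1.32 |

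With m = 10 instead of 8.5, power at 640 is 79.9%, 76.7%, 67.9% and 56.2% for the four ICCs.

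**Step 3: limits of the calculation.** The figures come from a two-proportion test. The planned acute-injury analysis is a Cox model on exposure hours to first injury, so they are a guide to it and not its exact operating characteristics. They also treat teams as if each had been randomised independently, which was not so.

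**The case against.** **The size of the loss is assumed.** The article gives no ICC, and at 0.01 power is still about 80%. A reader might infer that the trial cannot have its stated 80% power; the documents do not establish that. They show only that no allowance was made. The comfort at 0.01 is thin, however: it comes from dropping the continuity correction that the 640 needs in order to be reproduced.

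**The article is a condensed text.** A full protocol or SAP could specify a clustered variance. This has weight for the analysis half: the article does not say that players will be treated as independent, only that a Cox model with named covariates, and two-sample tests, will be used. It has no weight for the sample size, where clustering is set aside in the text itself.

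**Team is not the allocated unit.** Each arm is one region, so a difference between regions cannot be separated from an intervention effect. A reader might infer that a team frailty or clustered variance would restore a 5% error rate. It would not. This objection stands in full. It limits what the correction achieves but does not excuse ignoring team.

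**Competition level.** A reader might infer that leaving the matching factor out of the model is a further cause of narrow intervals. Omitting a balanced prognostic factor does not generally do that; in a Cox model it tends to pull the estimate towards the null. The case for including it is precision.

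**The 456 figures.** Much of that shortfall is not clustering: power there is about 69% even with independent players. The gap between 640 and 456 is a separate issue.

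**Conclusion.** The concern holds. The sample size leaves out clustering although the trial enrols teams, and neither stated analysis allows for it. The power cost at 640 enrolled runs from about 3 percentage points (ICC 0.01) to about 24 (ICC 0.10), measured from 83%. It becomes material somewhere between 0.02 and 0.05. A test that ignores team would have a type I error of roughly 6% to 14% in place of 5%.

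These sizes rest on the assumed ICC range, equal teams of 8.5 analysed players and the two-proportion approximation. Because of the one-region-per-arm allocation, they are best-case figures for this design.

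**What to change.** **Acute injury.** Fit the Cox model with a shared frailty for team, or with a team-clustered robust variance and a small-sample correction. Fix both age and gender as covariates in place of the open choice between them, and add competition level for precision.

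**Overuse injury.** Replace the plain t-test or Mann-Whitney test of mean prevalence with a comparison clustered by team.

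**Sample size.** Stop using the parenthesis on multiple cluster randomisation as the reason for omitting clustering. State the design effect 1 + (m − 1)×ICC over a stated ICC range, and restate power for the number actually enrolled. This does not call for enrolling more players.

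**Interpretation.** State that these steps address within-team correlation only, that the effect remains confounded with region, and that the conclusions carry this limit.

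**Cost.** Revised wording and a model option. No new data are needed, because players are enrolled by team and teams are matched on level. The price is wider intervals and a lower stated power.

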### Study design and allocation

A randomized prospective controlled trial with a follow-up period of one volleyball season (September, 2017 – June, 2018) will be conducted (Fig. 1). In The Netherlands, Nevobo organizes its recreational competitions in 4 different geographical regions and recreational teams compete against each other within a geographical region. For practical reasons, the two largest competition regions (geographical regions West and East) will be selected for the study and randomly assigned to an intervention region and a control region. This is done to avoid any contamination and competitive bias within a competition region. The expectation is that coaches might be more inclined to participate if the group allocation and thus the volleyball conditions (training and match) do not differ between teams within a competition region. The need for ethical approval was waived by the Medical Ethics Review Committee of the Academic Medical Center because the Medical Research Involving Human Subjects Act (WMO) does not apply to our study protocol (W17_048#17.065; Amsterdam, The Netherlands). The study protocol is registered in the Dutch Trial Registry (ID: NTR6202).

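### Teams are matched on competition level, but neither main comparison uses it: a probably modest precision gain is forgone and any remaining level imbalance would go unadjusted

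*Protocol article*

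**What the plan says.** All references are to the protocol article.

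- **Sample size:** "The teams within the intervention and control groups will be matched according to their competition level". No other matching factor is named.
- **Study design and allocation:** two competition regions are "randomly assigned to an intervention region and a control region", so each arm is one region.
- **Statistical analysis, acute injury:** "Differences in the incidence of acute injury between the intervention and control groups will be assessed using cox regression analysis", "adjusted for age and/or gender".
- **Statistical analysis, overuse injury:** the arms are compared by "comparing their mean prevalence (independent T-tests and/or Mann-Whitney test"). No covariate, stratum or pairing is mentioned.
- **Statistical analysis, baseline:** "To evaluate the success of the randomization and matching, baseline values will be analysed for differences between the intervention and control group", by chi-square, t or Mann-Whitney tests. This is the only place in that section where matching appears, and nothing in the later analysis depends on the result.
- **Statistical analysis, secondary:** these analyses are by level of adherence, not competition level.

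**The concern.** A factor chosen for matching is normally one thought to predict outcome, and the usual rule is to carry it into the analysis. Here it is dropped. The article names the covariates and the tests, so this is a stated choice and not a detail left to an analysis plan.

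Two things are at stake. First, a comparison that treats matched arms as unmatched does not use the balance when it estimates uncertainty. Second, if the enrolled teams end up unevenly spread over levels, nothing in the stated analysis takes that out of the effect. With only two regions randomised, randomisation cannot be relied on to balance team characteristics. Baseline significance tests can flag a difference but do not correct one.

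A smaller defect sits in the same sentence of the plan: and/or allows three Cox models (age, gender, or both).

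**Working it through.** **1. The plan's own figure.** Inputs from Sample size: control proportion 0.25, 40% reduction (0.25 × 0.6 = 0.15), 15% loss, and "To achieve 80% power with a significance level of 0.05". Two-sided testing is assumed, as sidedness is not stated.

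- n = [1.96·√(2·0.20·0.80) + 0.8416·√(0.25·0.75 + 0.15·0.85)]² / 0.10² = 250 per arm.
- With continuity correction: (250/4)·[1 + √(1 + 4/(250·0.10))]² = 270 per arm.
- With loss: 270/0.85 = 318 per arm, 636 in total, against the stated 640.

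The figure reproduces. Matching does not enter it, so this point does not change 640.

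**2. Precision forgone (illustration).** The article gives no injury rates by level. Assumed: three equally common levels balanced between arms, 320 × 0.85 = 272 evaluable players per arm, a 40% reduction at every level, a binary outcome on the risk-difference scale, and no team clustering.

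- Ignoring level: variance = (0.25·0.75 + 0.15·0.85)/272 = 0.315/272, SE 0.0340, power = Φ(0.10/0.0340 − 1.96) = 83.6%.
- Stratified by level: replace each p(1 − p) by its average within levels.

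| Assumed control rates by level | Variance ratio, stratified to unstratified | SE | Power |
|---|---|---|---|
| 0.20 / 0.25 / 0.30 | 0.993 | 0.0339 | 83.9% |
| 0.15 / 0.25 / 0.35 | 0.971 | 0.0335 | 84.7% |
| 0.10 / 0.25 / 0.40 | 0.935 | 0.0329 | 86.0% |

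The gain is about 0.3 to 2.4 points of power.

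**3. Effect of an imbalance, if one remained (illustration).** Same rates, with 5 or 10 percentage points of control players moved from the lowest-risk to the highest-risk level. Bias in the risk difference = shift × (highest − lowest rate).

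- Smallest case: 0.05 × 0.10 = 0.005. A true risk ratio of 0.60 appears as 0.15/0.255 = 0.588.
- Largest case: 0.10 × 0.30 = 0.030. It appears as 0.15/0.280 = 0.536.
- Moved the other way, the same cases give 0.15/0.245 = 0.612 and 0.15/0.220 = 0.682.

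A two-level version on the rate scale uses 0.60 × (b·r + 1 − b)/(a·r + 1 − a). Here a = 0.5 is the higher-level share in the control arm, b is the share in the intervention arm, and r is the rate ratio of higher to lower level.

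- b = 0.6: 0.60 × 1.30/1.25 = 0.62 (r = 1.5) and 0.60 × 1.60/1.50 = 0.64 (r = 2).
- b = 0.4: 0.60 × 1.20/1.25 = 0.58 and 0.60 × 1.40/1.50 = 0.56.

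**The case against.** The strongest reply is that matching has already done its main work. If teams are matched on level, the arms are balanced on level whether or not it is in the model. In an ordinary difference in means, omitting it makes the test somewhat conservative and does not bias the effect. This stands: a reader might infer that the benefit of matching is lost, but only the precision part is forgone.

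A reader might also infer that the effect will be biased, because 64 teams were planned and the Discussion reports 46 enrolled. The documents do not support that. Fewer teams is a smaller sample, not broken matching, and the Discussion does not describe the levels of the 46 teams. Bias needs both imperfect matching and a link between level and injury, and the article shows neither.

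A larger power gain can be computed from a team-level model, var(log RR) = [(1/m₀ + s²) + (1/m₁ + s²)]/32. Take m₀ = 0.2877 × 8.5 events per control team (0.2877 = −ln 0.75; 8.5 = 10 × 0.85), m₁ = 0.6·m₀ and an assumed between-team variance s² = 0.2. The SE is 0.216 and power 66%. If level explained 30% or 50% of s², the SE would be 0.207 or 0.201 and power 69% or 72%. The arithmetic is right, but the planned Cox model is at player level with no team term, so this gain belongs to an analysis the article does not contain. In a Cox model, moreover, a prognostic covariate generally does not shrink the SE of the treatment log hazard ratio. Any gain in power comes mainly from the estimate moving away from the null.

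Finally, one might read the baseline tests as a device for choosing covariates. The article does not say so.

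What the objection leaves untouched is that the stated analysis omits the matching factor and offers no remedy if balance on level fails.

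**Conclusion.** The point holds in limited form. Competition level is the matching factor, neither main comparison uses it, and the overuse comparison has no adjustment at all. The consequence is a forgone gain in precision or power, probably modest, and the lack of any step to remove a level imbalance should one exist. The illustrated sizes are 0.3 to 2.4 points of power, and 0.005 to 0.030 on the risk difference for a 5 to 10 point imbalance. They rest wholly on assumed rates by level and on an analysis without team clustering; the true size cannot be known from the article.

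This is a cheap improvement, not a demonstrated bias. It is second to two larger problems that it leaves unchanged: arm and region are fully confounded, and players are clustered in teams.

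**What to change.** - **Acute injury:** include competition level in the Cox model, as stratum or covariate, together with both age and gender. Fix this set in advance and delete the and/or.
- **Overuse injury:** replace the two-sample test of mean prevalence with a player-level repeated-measures regression on the 2-week reports, for example a logistic mixed model or GEE, with the same covariates. Mean prevalence per arm can stay as a descriptive summary.
- **Team clustering:** handle it separately in both models; adding level does not do this.

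**Cost.** A few degrees of freedom; the exact number depends on how many levels there are, which the article does not give. No new data should be needed, since level must be known in order to match on it and age and gender are already planned covariates. For acute injury the change is one of wording. For overuse injury it is a change of method, because the present summary is a group-level average into which a player or team covariate cannot enter. None of this removes the confounding from having one region per arm.
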